#### Patient-Reported Outcomes (Clinical)

A series of questionnaires with sound psychometric properties are to be used to assess general health and cancer-specific quality of life and cancer-related fatigue. The Medical Outcomes Study 36-Item Short-Form Health Survey (SF-36) is used to assess general health-related quality of life status across physical functioning, physical role functioning, bodily pain, general health, vitality, social functioning, emotional role functioning, and mental health domains (higher scores indicating a greater quality of life) [33]. Cancer-specific quality of life is evaluated by the core quality of life (QLQ-C-30) questionnaire developed by the European Organization for Research and Treatment of Cancer (EORTC) [34]. This questionnaire includes five functional domains (physical, role, cognitive, emotional, and social, with higher scores representing greater function/quality of life) and three symptom scales (fatigue, pain, and nausea, with lower scores indicating greater quality of life/less symptom severity). The General Health Questionnaire (GHQ-12) is administered to assess the psychological morbidity and possible psychiatric disorders [35]. Cancer-related fatigue is assessed using the Functional Assessment of Chronic Illness Therapy-Fatigue (FACIT-Fatigue) scale [36]. Finally, the Spanish version of the Alcohol Use Disorders Identification Test (AUDIT) is administered to screen for harmful alcohol consumption [37].

#### Overall Survival (Prospective Observations)

To assess survival, patients will be followed-up for 5 years. Overall survival will be measured from the time of randomization until death. Medical records and death certificates will be reviewed every year to obtain the survival status. The cause of death will be determined by reviewing medical and death records.

### Effectiveness: Secondary Study Outcomes

#### Anthropometry and Body Composition

The height will be measured using a wall stadiometer (Seca) and body composition with a bioimpedance analyzer (Inbody 770, In-Bldg). The participants will be seated in a quiet room for measuring the resting heart rate and blood pressure.

#### Blood Samples

A derivatives of reactive oxygen metabolites (d-ROMS) test will be performed to assess the levels of oxidative stress in the patients [38].

#### PA Levels

All patients randomly selected to have their PA assessed will be asked to wear an accelerometer (DynaPort MoveMonitor; McRoberts BV) for a full week. This will be fitted around the waist, with the sensor at the middle of the lower back, and should be worn throughout the waking hours, except during water-related activities (ie, swimming and showering). Further, patients are asked to complete a diary documenting the main PA they perform, how tired they feel, and how many hours they sleep each day. With these data, we will analyze the time spent performing moderate PA, time spent on sedentary activities, number of steps walked, and calories burned per day [39].

#### Health Economics

An economic evaluation will be performed in parallel with the trial to assess the health benefits, additional costs, and potential savings of including exercise therapy as a standard of care for patients with cancer. This health economics analysis will provide the relative value for money of exercise medicine compared with other health care interventions in this patient population, stratified by age, cancer type, point along the cancer continuum, and stage of the disease. Hospital resource usage and associated costs will also be assessed to compare the costs of secondary health care utilization between the intervention and reference (usual care+PVS) groups. All hospital events, including emergency department attendances and admissions, outpatient visits and procedures, and inpatient admissions for all causes will be explored to quantify and identify potential disease-related events, as well as the total health care resource use for all other purposes inclusive of comorbidities and other chronic diseases. The cost of providing the supervised exercise and PVS interventions will also be quantified. Health benefits will be measured in terms of the quality of life based on the SF-6D utility index derived from the SF-36 and converted to a health utility score to obtain quality-adjusted life years for cost-utility analysis [40].

#### Adverse Events

An external committee will review and compare all nonserious adverse events, whereas researchers will be obliged to report any serious adverse events to the research unit by email. A coordination committee with access to all the information it needs will undertake preliminary analyses of the data to monitor the safety of the program. This committee will be composed of individuals who are independent of the organization responsible for managing the study and members of the research team including the study coordinator; all are blind to patient allocation. In addition to serving on the committee, the coordinator will telephone the participating health centers daily to check on the progress of the study, report weekly on this progress to the principal investigator of the study, produce a monthly report with the study data, and provide recommendations to the study management team.

The trial was registered on January 18, 2019 (Clinical Trials.gov NCT03819595).The protocol has been approved by the local Clinical Research Ethics Committee (CEIC de Euskadi, PI2019016).

### Effectiveness: Additional Measures

#### Qualitative Evaluation

Knowledge generated by qualitative evaluation is essential for designing a tailored implementation strategy to address organizational and professional barriers that may hinder the adoption of the Bizi Orain program under routine conditions. The qualitative evaluation is designed around the use of focus groups to explore the perceptions of each population involved in the study: clinicians (oncology and hematology services), exercise instructors, community agents (local authorities, managers, and instructors of fitness centers), and patients. Briefly, 14 focus groups with 5-8 members each will be conducted to acquire a global and heterogeneous perspective of the Bizi Orain program: 1 for clinicians, 1 for exercise instructors, 6 for community agents (1 per exercise laboratory), and 6 for patients (1 per exercise laboratory). The moderation of the discussions is structured based on the Consolidated Framework for Implementation Research (CFIR) [41] and adapted to each population. This theoretical framework is a valuable instrument to detect and analyze barriers and facilitators. This framework differentiates 39 constructs, organized into 5 domains or dimensions, which influence the degree of the real implementation of a program or intervention. Specifically, the 5 domains of the CFIR are the following: “characteristics of the intervention,” “external context,” “internal context,” “characteristics of the individuals involved,” and “implementation process.” Owing to the need for intervention on contextual factors—a key element in the design of any implementation strategy—and promotion of cooperation between health organizations and the community, the CFIR adapts to the analytical needs of this evaluation. In addition, the research team will adopt an inductive perspective to favor the emergence of concepts and issues not covered by this theoretical framework, which are key to understanding the mechanisms of Bizi Orain. The discourse generated in each group will be audio-recorded and transcribed verbatim. Moreover, the moderator and observer will prepare notes during the fieldwork to complete and triangulate the recorded data.

Qualitative data analysis will be structured into three stages. First, a deductive analysis will be conducted to identify the constructs of the theoretical framework that influence the implementation of the Bizi Orain program. Second, an inductive analysis based on grounded theory [42] will be conducted to identify other emergent categories that have an impact on the program. Finally, a qualitative comparative analysis will be performed to identify the necessary and sufficient variables needed to improve the implementation of the Bizi Orain program in primary care exercise laboratories. Atlas Ti software (version 5.0, ATLAS.ti Scientific Software Development GmbH) will be used to analyze the qualitative data.

#### Exercise Intervention

The program operates throughout the year and is a free 12-week, small-group (~8 people) exercise program supervised by specially trained instructors. Participants are required to participate in supervised exercise twice a week and to exercise independently a third time, walking in the neighborhood of the health center at a given target exercise intensity. Carers of eligible participants are invited to attend the program with the care recipients.

#### Individual Consultations

Before commencing the program, each participant receives a one-on-one consultation with an exercise physiologist at Deusto University. This consultation involves screening of the health status and initial assessments to tailor the exercise prescription according to the type of cancer, stage and treatment history, severity of symptoms/adverse effects, comorbidities, PA habits, and personal preferences. Each participant’s exercise program is designed to provide optimal stimulus to the cardiorespiratory and neuromuscular systems while maximizing safety, compliance, and retention. Subsequently, patients return for further consultations to undergo assessments and assess their progress since initiating the program, discuss strategies to continue exercising after the program, and develop a plan to maintain long-term positive exercise behavior.

#### Group Exercise Sessions

Exercise sessions twice a week are conducted in groups of approximately 8 participants under the supervision of an accredited exercise physiologist or a nurse in the Bizi Orain exercise laboratories at the local health centers. The sessions last approximately 1-1¼ h and include a combination of moderate-to-high intensity aerobic and resistance exercises. The aerobic exercise component includes 30-35 min of at least moderate-intensity cardiovascular exercise using cycle ergometers and treadmills. The exercise intensity increases from moderate intensity for 8-min periods alternating with 2-min lower-intensity periods during the first month, moving toward higher-intensity 5-min intervals by the third month (Figure 2).

The exercise intensity zones are tailored to each patient by the estimated maximum heart rate using the equation 206.9 – (0.67 × age) [43] and applying specific intensity boundaries based on the HRR, defined as the difference between the resting heart rate and maximum heart rate. The %HRR has been adopted by the American College of Sports Medicine as the gold standard for indirect assessment of exercise intensity [44]. Every exercise session will be monitored with a heart rate monitor, teaching the patients to self-manage their exercise sessions with respect to the prescribed target intensities. The target intensity is between 40% and 85% of the HRR [44]. The perceived level of effort is recorded using the Borg RPE scale from 0 (rest) to 10 (maximal effort) [45], with the target intensity progressively increasing from 3 to 5-6 points (Table 1).

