### Program Design

Bizi Orain is a hybrid two-stage study. During the first 3 months, the study has a parallel-group randomized controlled clinical trial design, where study participants are randomly allocated (1:1) to either the Bizi Orain exercise program in addition to a previously reported behavioral intervention [23,24] for the promotion of healthy habits, or to the Prescribe Vida Saludable (PVS) group (In Spanish, “Prescribe Vida Saludable” means “prescription of healthy habits”) alone. After the postprogram assessments, participants allocated to the PVS group will initiate the Bizi Orain exercise program. Thereafter, a 5-year prospective observational cohort study will be conducted with follow-ups at 3, 6, 12, 24, 36, 48, and 60 months (Figure 1) to (1) examine the long-term clinical effects of PA exposure on overall survival, physical function, and patient-reported outcomes and (2) evaluate the feasibility of Bizi Orain, identifying potential barriers and facilitators for a generalized and sustainable exercise program within standard health care settings. To address this point, a qualitative research study will be conducted involving clinical, research, administrative, and community staff, and patients with cancer.

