### Randomization

Patients will be centrally randomized by PCRUB-BBRI in a 1:1 ratio into the two study groups. A researcher who is independent of the organization responsible for managing the study will randomly allocate patients to groups using a computer-based random number generator.

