Participants undertake additional group-based walking (“park walking”) exercises, progressing from 30 min at low-to-moderate intensities to 40 min at moderate intensities. These walking sessions are self-managed by participants based on the perceived effort and heart rate. Patients’ carers are invited to attend these sessions. These strategies (ie, leadership, independence, and carer involvement) are based on the theory of planned behavior [48] and are designed to change attitudes toward exercise, increase perceived behavioral control, and influence the subjective norms or the social factors. We believe that if patients find these sessions are enjoyable, the long-term adherence will be higher, and this will have a significant impact on the long-term study outcomes.

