**Statistical Analysis**

Data will be analyzed on an intention-to-treat basis with the maximum likelihood imputation of missing values, comparing average change scores at 3 months of follow-up (postintervention) among participants randomly assigned to the Bizi Orain or PVS groups. These analyses will include standard descriptive statistics, Student *t* tests, and analysis of covariance models adjusted for baseline values. These models will be extended to include clinically relevant covariates. Subgroup analyses will be conducted by cancer site and treatment status. Investigations into responders and nonresponders will be conducted to explore the heterogeneity of the intervention effect. To analyze the association between changes in the PA over time and outcome variables, longitudinal mixed-effects models will be used for repeated measures throughout the 5 years of follow-ups. Cox proportional hazards models will be used for survival analysis. No imputation method will be used to handle missing data as longitudinal mixed-effect models based on maximum likelihood estimation are more appropriate to handle missing data [49] than common imputation methods such as the last observation carried forward, complete case analysis, or other possible forms of imputation.

Finally, the incremental cost-effectiveness, cost-utility ratios, and confidence intervals will be calculated through bootstrapping and sensitivity analyses. All the analyses will be performed with SAS (version 9.4, SAS Institute) and R (version 3.6, R Core Team) statistical packages.

We have a network of 6 exercise laboratories with a capacity to include at least 1013 patients during the 2 years of recruitment. Assuming a 30% rate of loss (including deaths) throughout the year of follow-up, the study has a power of 80% to detect a difference in functional capacity between comparison groups, of at least 9 s in the 400-m walk test at 3 months as significant (α=.05), assuming a standard deviation of 95 m. Regarding the quality of life, the study has a power of over 90% to detect differences of 5 points between groups as significant (α=.05).

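### Before the 3-month comparison only the Bizi Orain arm is treated in groups, yet the planned tests and power treat all patients as independent; if outcomes correlate within group, the standard error will be too small

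*Protocol article*

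**What the plan says.** - **Allocation** (Randomization): "Patients will be centrally randomized by PCRUB-BBRI in a 1:1 ratio into the two study groups". The unit is the patient.
- **Delivery in the exercise arm** (Group Exercise Sessions): the two weekly supervised sessions are "conducted in groups of approximately 8 participants under the supervision of an accredited exercise physiologist or a nurse". The text after Table 1 adds: "Participants undertake additional group-based walking". That paragraph says the walking strategies are meant to act on attitudes and on social influences. Exercise Intervention also gives a group size of about 8 over 12 weeks.
- **Comparator** (Program Design): "After the postprogram assessments, participants allocated to the PVS group will initiate the Bizi Orain exercise program". At the 3-month comparison, PVS patients have not yet been in an exercise group.
- **Analysis** (Statistical Analysis): change at 3 months is compared by Student t tests and "analysis of covariance models adjusted for baseline values", with clinically relevant covariates as the only stated extension. Mixed models are named only for repeated measures over the 5 years.
- **Power** (Statistical Analysis): "We have a network of 6 exercise laboratories with a capacity to include at least 1013 patients during the 2 years of recruitment", and "Assuming a 30% rate of loss (including deaths) throughout the year of follow-up". The article claims 80% power for 9 s on the 400-m walk with an SD printed as 95 m, and over 90% for 5 points in quality of life. No ICC or design effect appears.

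**The concern.** Individual randomization makes patients independent at allocation. It does not keep them independent once one arm is treated in shared groups. Patients who train together share a supervisor, a room, a schedule and each other's company, and the protocol treats social influence as part of how the programme works. Some positive within-group correlation in 3-month outcomes is therefore plausible in the Bizi Orain arm, with no counterpart from exercise groups in the PVS arm.

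A t test or ANCOVA without a group term would then understate the variance of the exercise-arm mean. Confidence intervals would be too narrow, the type I error would exceed 5%, and the stated power would be too high. This applies to physical function and to quality of life, which are both primary outcomes of the randomized phase.

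**Working it through.** **Inputs from the article:** N = 1013; loss 30%; difference 9; SD 95; α = 0.05, with sidedness not stated and taken as two-sided; group size m about 8; 6 laboratories.

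**Assumed:** an ICC of 0.01 to 0.10 (the article gives none), and equal total variance in the two arms.

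**1. The plan's own power figure.**
- Evaluable per arm: 1013 × 0.7 / 2 = 354.55.
- Standard error of the difference under independence: 95 × √(2/354.55) = 7.135.
- Power for 9 units: Φ(9/7.135 − 1.96) = Φ(−0.70) = 24.2%, not 80%.
- Difference with 80% power: 2.802 × 7.135 = 20.0.

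The stated 80% does not reproduce from 9 s and SD 95 m. With N = 1013, 30% loss and SD 95, it fits a difference of 20 with a design effect of exactly 1. That is consistent with a calculation that assumes independent patients. The mismatch between 9 s and 95 m is a separate defect and is not caused by clustering. The power figures below therefore start from a nominal 80%, not from a figure that the printed inputs support.

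**2. Partially nested design effect.**
- Exercise-arm variance is multiplied by 1 + (m − 1)·ICC; PVS-arm variance by 1.
- Variance of the difference is multiplied by f = 1 + (m − 1)·ICC/2.
- Actual type I error: 2·[1 − Φ(1.96/√f)].
- Actual power from a nominal 80%: Φ(2.802/√f − 1.96).
- N to restore the nominal power: 1013 × f.

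| m | ICC | f | Type I error | 80% becomes | N needed |
|---|---|---|---|---|---|
| 8 | 0.01 | 1.035 | 5.4% | 78.6% | 1049 |
| 8 | 0.02 | 1.070 | 5.8% | 77.3% | 1084 |
| 8 | 0.05 | 1.175 | 7.1% | 73.4% | 1191 |
| 8 | 0.10 | 1.350 | 9.2% | 67.4% | 1368 |
| 5.6 | 0.01 | 1.023 | 5.3% | 79.1% | 1037 |
| 5.6 | 0.02 | 1.046 | 5.5% | 78.2% | 1060 |
| 5.6 | 0.05 | 1.115 | 6.3% | 75.6% | 1130 |
| 5.6 | 0.10 | 1.230 | 7.7% | 71.4% | 1246 |

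Here m = 5.6 is 8 × 0.7. The 30% loss is stated for a year, so the size that applies at 3 months probably lies between 5.6 and 8.

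**3. What would make it smaller.** If delayed PVS patients later fill half the places in each group (an assumption), m is 4, or 2.8 after loss. At m = 2.8 and ICC 0.10, f = 1 + 1.8 × 0.10/2 = 1.09, type I error is about 6% and power about 77%.

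**4. What would make it larger.** Suppose a laboratory or instructor effect exists in the exercise arm only. With 354.55/6 = 59.1 evaluable exercise patients per laboratory, an ICC of only 0.01 gives f = 1 + 58.1 × 0.01/2 = 1.29, type I error 8.4% and power 69%. With six laboratories the normal approximation is rough, so this is only an indication of size.

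**The case against.** **The ICC may be near zero.** The article gives none, and much of the programme is individual: prescriptions are tailored to disease, treatment and symptoms, heart-rate zones are set per patient, and resistance load follows each patient's own level of effort. The walks are self-managed, and Exercise Intervention describes the third weekly session as independent exercise. This stands: the error is conditional on a positive ICC, and at 0.01 it is small.

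**Closed groups with one instructor are not stated.** The programme runs all year, which allows rolling entry, and delayed patients may join the same groups. This also stands. It lowers the effective m and affects which unit the model should use.

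**A reader might infer that six laboratories by themselves make the standard error too small** ("We have a network of 6 exercise laboratories"). The article does not support that. Randomization is individual, so laboratory differences shared by both arms do not inflate the error of the difference. Only effects confined to the exercise arm do.

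**A reader might also infer that the trial's real power falls from 80% to a given figure.** That cannot be said, because the printed inputs do not give 80% to begin with.

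**The model detail may sit in an unseen SAP, and PVS counselling could cluster by clinician in both arms.** Degrees of freedom and random-effect structure can be left to an SAP. But the article does name the 3-month tests and gives a power statement without any allowance for grouping, so it is not silent. Clinician clustering is possible, but it does not remove the extra grouping in the exercise arm.

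**Conclusion.** The concern holds as a conditional one. Before the 3-month comparison the design is partially nested, and the stated tests and power make no allowance for it. If outcomes correlate within exercise group or instructor, the standard error will be too small for both primary comparisons. The documents do not show that it is too small, because they give no ICC.

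Over an assumed ICC of 0.01 to 0.10 the effect runs from negligible to moderate, as the table shows; at 0.05 with 8 per group, type I error is 7.1% and a nominal 80% power becomes 73.4%. These figures rest on groups that consist of immediate-arm patients only, equal total variance in the arms, and no further instructor or laboratory effect in the exercise arm. The correction is worthwhile mainly because it is cheap and depends on data that may be impossible to recover if they are not recorded during delivery.

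**What to change.** 1. **Record the grouping.** Add exercise group and instructor to the session attendance data that the Adherence section already tracks.
2. **Change the 3-month model.** Keep the baseline-adjusted comparison, and add a random effect for exercise group in the Bizi Orain arm only. If membership rolls, use instructor within laboratory instead. Use small-sample degrees of freedom (Satterthwaite or Kenward-Roger). A laboratory main effect is optional and is not needed to correct the standard error.
3. **Restate the power.** Give an assumed ICC with a range, and multiply the variance of the difference by 1 + (m − 1)·ICC/2. The mismatch between 9 s and an SD in metres has to be resolved separately before any restated power means anything.

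Cost: two recorded fields and one model term, slightly wider confidence intervals, and a less favourable stated power.
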